**Fig 1 pone.0316028.g001:**
[figure not shown]
Study flow chart. Note: FI, first implantation; RIF, Recurrent implantation failure; ET, embryo transfer.

**Fig 2 pone.0316028.g002:**
[figure not shown]
The schedule of enrolment, interventions, and assessments. Note: *-t1: Eligibility screen and informed consent before frozen embryo transfer; 0: Allocation at the beginning of frozen embryo; t1: Ultrasound analysis at the day before embryo transfer; t2: Biochemical pregnancy at 14 days following embryo transfer; t3: Clinical pregnancy and embryo implantation at 28 days after embryo transfer.

### Participants and sample size

#### Diagnostic criteria for RIF patients

According to the definition of RIF proposed by EHSRE 2023 [12], the transfer of embryos considered viable fails to result in a positive pregnancy test for a given patient and is insufficient to consider further investigation and/or intervention. Considering that the recommended threshold for the cumulative predicted chance of implantation for RIF is 60%, when a couple does not successfully implant by transferring a certain number of embryos and the cumulative predicted chance of implantation associated with that number is greater than 60%, then they should be advised to undergo further investigations and/or treatment options.

For embryos of unknown euploidy [13], RIF is diagnosed in female patients under 35 years old after three or more embryo transfers (ET); for those aged 35 to 39, after four or more ETs; and for those aged 40 and above, after six or more ETs. For embryos with known ploidy status [14], RIF is diagnosed after two or more ETs.

#### Diagnostic criteria for FI patients

FI patients are defined as patients who have not previously undergone fresh or frozen embryo transfer.

#### Inclusion criteria

Patients met all four following criteria will be included.

Aged between 21 to 45 years who are undergoing FET;Diagnosed as FI or RIF patients;Using the hormone replacement treatment (HRT) or a GnRH-a down-regulating hormone replacement protocol for FET endometrial preparation;Signing an informed consent form.

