This study, grounded in a current cross-sectional investigation employing support vector classification (SVC) algorithms, aims to explore: (1) the predictive precision of MV-FLOW^™^ endometrial vascular distribution indices and/or endometrial vascular indices for FET outcomes in RIF patients; (2) the potential of these indices to categorize patients as either successful first implantation (FI) or RIF.

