## Methods and materials

### Study design

We will recruit a cross-sectional observational cohort of FI and RIF patients from Jinxin Sinan Women’s and Children’s Hospital in Sichuan who underwent FET. These patients will undergo transvaginal ultrasound examination, including assessment of endometrial MV-FLOW^™^ prior to embryo transfer in FET. First, the foundational clinical data of RIF patients, along with endometrial ultrasound-related indices, will serve as features to forecast the clinical outcome of FET. Subsequently, a clinical prediction model grounded in multidimensional ultrasound features will be developed. The efficacy of this model will be rigorously assessed and subjected to cross validation. Then, the characteristics observed under transvaginal ultrasound examination in successful FI and RIF patients will be employed as predictive indicators to ascertain whether they can effectively categorize successful FI and RIF patients post-transplantation. The dates of the recruitment are July 15^th^, 2024 to July 15^th^, 2025. We will also establish a flexible recruitment timeline, allowing for adjustments as needed, and regularly monitor and evaluate the recruitment progress, enabling us to identify and address any issues promptly. All obtained private data will be subject to the supervision of the ethics committee, and the study will be conducted after patients have signed the informed consent form. This trial was reviewed by the ethics committee of Sichuan Jinxin Xi’nan Women’s and Children’s Hospital (2023–006), and registered in Chinese Clinical Trial Registry (ChiCTR2400086401) (See S1 Table). Study flow chart see Figs 1 and 2 and S2 Table (the SPIRIT schedule of enrollment).

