#### Sample size calculation

This study is a cross-sectional trial to establish a predictive model for endometrial receptivity and pregnancy outcomes using SVC to predict clinical pregnancy. The ultrasound assessments of uterine arteries and endometrial thickness are crucial for pre-implantation evaluation of endometrial receptivity, a study involving 78 FET patients (resulting in 45 clinical pregnancies, 57.7%) utilized elastic ultrasound imaging and nine predictive indicators based on basic information, achieving a predictive accuracy of 76.92% [15]. Sample size estimation was conducted using “pmsampsize” in R software [16]. According to the definition of RIF, at least two failed ETs were diagnosed as RIF. Assuming a clinical pregnancy rate of 30%, a minimum of 323 RIF patients were required for sample estimation. In a 1:1 ratio, 323 FI patients were also included. The code for sample size calculation is referenced in S1 Fig.

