### Clinical data acquisition

We will systematically compily comprehensive clinical data for RIF or FI patients, encompassing their foundational details such as chief complaints, present illness history, past medical history, family history, allergy history, pertinent examination findings, comorbid conditions, and medication use. Additionally, we will meticulously document their prior clinical information from assisted reproductive technology (ART) treatments, including treatment protocols, cycle specifics, and outcomes.

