### Data analysis

#### Data statistics

Data analysis was conducted using the SAS 9.4 statistical software (SAS Institute, Cary, NC, USA) by an independent statistician. Comparisons between the two groups will be performed as follows. For quantitative data, independent sample t-tests, analysis of variance, or Kruskal-Wallis H tests were employed; for categorical data, chi-square tests or Fisher’s exact probability method were utilized. All statistical analyses are two-sided, with *P* < 0.05 considered statistically significant.

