However, most prior studies have relied on retrospective analysis, potentially yielding biased results. Hence, prospective research remains essential to evaluate the feasibility and precision of ultrasound-derived uterine blood flow parameters in predicting the optimal embryo transfer timing in IVF. This protocol outlines a prospective, cross-sectional study that explores the role of ultrasound in pre-embryo transfer diagnostics. Building on this, we have pioneered the use of MV-FLOW^™^ to detect microvascular distribution within the endometrium and sub-endometrium, and validated its feasibility in assessing endometrial vasculature [11]. SVC [25] is a common supervised machine learning algorithm that seeks an optimal hyperplane in feature space to discriminate between different classes, characterized by excellent generalization capabilities. We propose to input all ultrasound-derived uterine blood flow parameters as flow features to predict embryo implantation outcomes and rates, thereby identifying the most predictive ultrasound indices for embryo implantation and discussing the diagnostic value of MV-FLOW^™^ in assessing endometrial receptivity. RIF is predominantly influenced by embryonic or uterine factors, with studies indicating abnormal blood flow parameters [26]. Our study extends this by investigating the clinical utility of these parameters in differentiating between successful first-time transfers and RIF cases, offering predictive markers for RIF identification.

In conclusion, while we have discussed the potential effects of MV-FLOW^™^ in predicting frozen embryo transfer outcomes in patients with recurrent implantation failure, it is important to consider the broader clinical implications should our study’s predictions prove accurate. Successful prediction models could revolutionize personalized treatment plans, allowing clinicians to tailor interventions more effectively and improve overall success rates in assisted reproductive technologies. This could lead to a paradigm shift in how recurrent implantation failure is managed, ultimately enhancing patient outcomes and satisfaction. Furthermore, the integration of MV-FLOW^™^ with multidimensional ultrasound features could pave the way for more comprehensive diagnostic tools, offering deeper insights into the underlying causes of implantation failure and facilitating more targeted therapeutic strategies.

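### The successful-FI versus RIF classification rests on ultrasound features while pooling two non-randomised preparation regimens, with no stated control for regimen or age, so part of any separation may not reflect RIF

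*Protocol article*

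**What the plan says.** Under Inclusion criteria, the protocol article accepts two preparation regimens in both patient groups: "Using the hormone replacement treatment (HRT) or a GnRH-a down-regulating hormone replacement protocol for FET endometrial preparation".

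Under Study design, the two models have different inputs. For the outcome model in RIF patients, "the foundational clinical data of RIF patients, along with endometrial ultrasound-related indices, will serve as features to forecast the clinical outcome of FET". For the second step, "the characteristics observed under transvaginal ultrasound examination in successful FI and RIF patients will be employed as predictive indicators". The Introduction words the second aim in the same way, as "the potential of these indices to categorize patients as either successful first implantation (FI) or RIF", where the indices are those from MV-FLOW. The Discussion states the intended use of the result: "offering predictive markers for RIF identification".

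Clinical data acquisition covers medication use and, for prior ART treatment, records "including treatment protocols, cycle specifics, and outcomes". Regimen and age are not named as a feature, matching factor or stratum in the FI-versus-RIF step. Sample size calculation fixes only a 1:1 ratio of FI to RIF patients. For quantitative data, Data statistics lists unadjusted two-group comparisons: "independent sample t-tests, analysis of variance, or Kruskal-Wallis H tests were employed".

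**The concern.** The scan is taken the day before transfer (note to Fig 2), when preparation is already under way, and the study is observational, so regimen is not randomised. A regimen that changes endometrial thickness or flow, and is used more often in one group, would produce an ultrasound difference between the groups even if RIF had no bearing on the endometrium. If regimen is chosen because of earlier failures, the difference would be a consequence of treatment and not a marker of RIF.

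Age is a possible second confounder. The comparison selects FI patients on success and RIF patients on repeated failure, and both selections may depend on age.

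This matters because RIF status is already known from the transfer history (Diagnostic criteria for RIF patients), so nobody needs a scan to assign it. The value of the second aim lies in interpretation, namely that MV-FLOW and related indices mark something about RIF. That reading weakens to the extent that the separation comes from regimen or age.

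**Working it through.** **The plan's own figure.** Sample size calculation says: "Assuming a clinical pregnancy rate of 30%, a minimum of 323 RIF patients were required for sample estimation". With the criterion for precise estimation of overall risk and an assumed margin of 0.05 (the code in S1 Fig is not shown), n = (1.96/0.05)² × 0.30 × 0.70 = 322.7, so 323. The figure reproduces. It concerns the outcome model in RIF patients and is unaffected by this point.

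**Inputs.** From the article: two pooled regimens, 323 RIF and 323 FI patients, and a contrast restricted to successful FI patients. Assumed, because the article is silent: GnRH-a shares of b = 30% in successful FI and a = 50% to 70% in RIF; a standardised regimen effect d of 0.5 or 1.5 on one ultrasound score; no true RIF effect. The number of successful FI patients is also not given. Applying 30% (the article's rate for RIF) to 57.7% (the rate in the 78-patient study it cites) gives 323 × 0.30 = 97 to 323 × 0.577 = 186.

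**Spurious AUC.** For one normally distributed score, AUC = 0.5 + (a − b) × (Φ(d/√2) − 0.5).

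- d = 0.5: Φ(0.354) − 0.5 = 0.138
- d = 1.5: Φ(1.061) − 0.5 = 0.356

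| GnRH-a share, RIF vs successful FI | d = 0.5 | d = 1.5 | Ceiling 0.5 + (a − b)/2 |
|---|---|---|---|
| equal | 0.500 | 0.500 | 0.50 |
| 50% vs 30% | 0.5 + 0.2 × 0.138 = 0.528 | 0.5 + 0.2 × 0.356 = 0.571 | 0.60 |
| 70% vs 30% | 0.5 + 0.4 × 0.138 = 0.555 | 0.5 + 0.4 × 0.356 = 0.642 | 0.70 |

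The ceiling is the AUC of regimen itself. Several indices combined could exceed the single-score values but not the ceiling.

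**Compared with chance variation.** The null standard error of an AUC is √((n1 + n2 + 1)/(12 n1 n2)).

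- 323 vs 97: √(421/375,972) = 0.0335, so an AUC above 0.5 + 1.96 × 0.0335 = 0.566 differs from 0.5 at the two-sided 5% level.
- 323 vs 186: √(510/720,936) = 0.0266, so the threshold is 0.552.

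A spurious AUC of 0.528 lies below both thresholds, and 0.555 lies between them. Both values for d = 1.5 (0.571 and 0.642) exceed both thresholds.

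**Unadjusted tests.** Suppose the listed tests are applied to one feature at 323 vs 186. The mean shift is d(a − b), and its standard error is √((1 + d²a(1 − a))/323 + (1 + d²b(1 − b))/186). For d = 0.5 and 50% vs 30%, this is 0.10/0.0946 = 1.06, a rejection rate of about 18% instead of 5%. For d = 0.5 and 70% vs 30%, it is 0.20/0.0944 = 2.12, about 56%.

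**Internal validation.** Model performance evaluation splits the data 7:3 and cross-validates. Any regimen or age imbalance is present in both parts, so neither step can show that the separation comes from it.

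**The case against.** The strongest reply is that bias needs two things the article does not document: different regimen use in successful FI and RIF, and a regimen effect on the indices. That stands. The text supports only that the classifier could pick up regimen. A reader might infer that it will, or that all the separation is spurious, and neither follows. The article gives only indirect support for the second condition. Its Discussion says endometrial flow rises from the proliferative to the secretory phase, and its Introduction reports that MV-FLOW responds at once to acupuncture.

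A reader might also take 0.60 to 0.70 as the expected spurious AUC. That range is the ceiling, reached only if the ultrasound score identified regimen perfectly.

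A further tempting inference is that the age-tiered RIF criteria make RIF patients older. They do not settle this. They require three, four or six transfers as age rises, so qualifying becomes harder for older women, and the net direction cannot be derived. No section links age to the ultrasound indices.

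Finally, a journal article may leave adjustment to a fuller plan, and its wording does not expressly exclude other features. This lowers the weight of the point but does not remove it. The article does fix the inputs, giving clinical data to the outcome model and describing the classification through ultrasound characteristics. The Abstract's mention of clinical features goes with clinical pregnancy as the label, so it describes the outcome model.

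**Conclusion.** The point holds as a conditional one. As described, the second aim could credit MV-FLOW with separation that is due to regimen or age, and nothing stated would reveal it. The size is unknown. Under the assumed shares and no true RIF effect, a single score would show an AUC of about 0.53 to 0.56 for a standardised effect of 0.5 and 0.57 to 0.64 for an effect of 1.5. With balanced use it would be 0.50. A modest imbalance therefore gives a small bias. Age is a possible confounder of undetermined direction. The case for changing the analysis rests on how cheap the change is, not on evidence that bias is present. No view is taken on which regimen should be used.

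**What to change.** For the second aim, fit a reference model with age and regimen only and report its AUC. Then report the gain in AUC from adding the ultrasound and MV-FLOW features, using the same cross-validation folds, and base the claim about RIF markers on that gain. Adding regimen as one more feature and reporting only the total AUC would not help, because the classifier could then use regimen directly.

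As supportive results only, give the ultrasound AUC within each regimen, cross-validated over all patients. Assuming 30% of 97 to 186 successful FI patients (29 to 56) and 50% of RIF patients (162) in the GnRH-a stratum, the null 95% half-width is 1.96 × √(192/56,376) = 0.11 to 1.96 × √(219/108,864) = 0.09. In the 30% validation set alone, with 9 to 17 against 49 patients, it would be about 0.21 to 0.16. Neither can resolve a spurious AUC of 0.53 to 0.56.

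The cost is one or two extra model fits, a possibly smaller headline result, and imprecise within-regimen estimates. No new data are needed, since regimen and age must both be known to apply the inclusion criteria.

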#### Exclusion criteria

Patients met any one of the following criteria will be excluded.

Diagnosed as severe primary or secondary conditions in the active phase, or mental disorders;Diagnosed with significant, untreated uterine malformations impacting uterine morphology, uterine fibroids exerting pressure on the uterine cavity, or ovarian cysts, as delineated by ultrasound;History of malignant neoplasms in any anatomical location;Presence of chromosomal abnormalities (excluding chromosomal polymorphisms).

#### Sample size calculation

This study is a cross-sectional trial to establish a predictive model for endometrial receptivity and pregnancy outcomes using SVC to predict clinical pregnancy. The ultrasound assessments of uterine arteries and endometrial thickness are crucial for pre-implantation evaluation of endometrial receptivity, a study involving 78 FET patients (resulting in 45 clinical pregnancies, 57.7%) utilized elastic ultrasound imaging and nine predictive indicators based on basic information, achieving a predictive accuracy of 76.92% [15]. Sample size estimation was conducted using “pmsampsize” in R software [16]. According to the definition of RIF, at least two failed ETs were diagnosed as RIF. Assuming a clinical pregnancy rate of 30%, a minimum of 323 RIF patients were required for sample estimation. In a 1:1 ratio, 323 FI patients were also included. The code for sample size calculation is referenced in S1 Fig.

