#### Ultrasound acquisition patterns and content

*2D ultrasound pattern*. In the two-dimensional grayscale mode, measurements of endometrial thickness, endometrial morphology, and endometrial motion will be conducted. Endometrial thickness will be determined by averaging three measurements of the distance between the anterior and posterior myometrium-endometrium interfaces, taken 1 cm from the endometrial apex. Detailed observation of endometrial echogenicity will be conducted, and the endometrium will be categorized into types A, B, and C based on the Gonen criteria [17]. Endometrial wave motion will be observed and documented for three minutes on the longitudinal midline section of the uterus with the probe stabilized and the patient breathing normally. Endometrial motion is classified into positive wave, negative wave, quiescent wave, bidirectional wave, local peristaltic wave according to the Ljland criteria [18].

In the two-dimensional color mode, with the uterus longitudinally bisected along its midline axis, the subendometrial region is demarcated as extending 3mm beyond the endometrial margin. Utilizing two-dimensional color Doppler flow imaging (CDFI), the perfusion of the endometrium and subendometrial areas will be assessed, classifying the flow patterns into Type I, II, and III according to the Applebaum criteria [7]. Subsequently, the CDFI is employed to delineate the uterine sagittal section, orthogonal to the long axis of the uterine cavity, where blood flow measurements are conducted. The color imaging technique is used to visualize the uterine arteries, with the sampling gate sequentially positioned at the cervix, both sides of the corpus, and the junction of the myometrium and endometrium to obtain stable blood flow spectrograms. Measurements are taken only after a minimum of consecutive stable waveforms are observed. The resultant parameters of uterine arterial blood flow encompass the peak systolic velocity (PSV), end diastolic velocity (EDV), time-averaged maximum velocity (TAMV), time-averaged peak velocity (TAPV), mean pressure gradient (PGmean), systolic/diastolic ratio (S/D), resistivity index (RI), and pulsatility index (PI).

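### The minimum of 323 RIF patients matches the criterion for precision of the overall pregnancy rate; by the same tool's other criteria it is too small for the ultrasound features the plan lists

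*Protocol article*

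**What the plan says.** The Sample size calculation section of the protocol article names the tool ("Sample size estimation was conducted using “pmsampsize” in R software") and gives the result: "Assuming a clinical pregnancy rate of 30%, a minimum of 323 RIF patients were required for sample estimation". It states neither a number of candidate predictors nor an anticipated R² or C-statistic. For those inputs the reader is sent elsewhere: "The code for sample size calculation is referenced in S1 Fig". The only nearby figures come from a cited study of 78 patients: "nine predictive indicators based on basic information, achieving a predictive accuracy of 76.92" per cent.

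The features are described in other sections. Ultrasound acquisition patterns and content lists grey-scale, colour Doppler, MV-FLOW and 3D measurements. One group begins "The resultant parameters of uterine arterial blood flow encompass the peak systolic velocity (PSV), end diastolic velocity (EDV" and continues to eight indices in all. The Discussion adds: "We propose to input all ultrasound-derived uterine blood flow parameters as flow features". Study design says that clinical data also enter the outcome model, which is built on RIF patients.

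Clinical prediction model describes a screen on Spearman correlation with clinical pregnancy, removal of low-variance and highly correlated variables, and a 7:3 split into training and internal validation sets.

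**The concern.** For a binary outcome pmsampsize returns the largest of three sample sizes. One limits overfitting (expected shrinkage at least 0.9), one limits optimism in Nagelkerke R² (at most 0.05), and one fixes the precision of the average risk (±0.05). The first two grow in proportion to the number of candidate parameters. The third does not depend on that number.

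The stated 323 coincides with the third. A reader will take it as the minimum for the prediction model, because the section presents it that way. If the other two criteria ask for more with the features actually listed, the sample lacks the property claimed for it, and this bears on the model that carries the study's main result.

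**Working it through.** **Reproducing 323.** The outcome proportion is 0.30 (Sample size calculation); the margin of ±0.05 is the tool's usual setting.

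n = (1.96/0.05)² × 0.30 × 0.70 = 322.69, rounded up to 323. The match is exact and uses no predictor count or model performance.

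**Counting candidates** (Ultrasound acquisition patterns and content). A variable with k categories takes k − 1 parameters.

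| Group | Variables | Parameters |
|---|---|---|
| Thickness | 1 | 1 |
| Morphology (3 types) | 1 | 2 |
| Wave motion (5 types) | 1 | 4 |
| Doppler flow type (3 types) | 1 | 2 |
| Uterine artery indices | 8 | 8 |
| MV-FLOW index | 1 | 1 |
| 3D: volume, VI, FI, VFI | 4 | 4 |
| **Total** | **17** | **22** |

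The clinical features come on top, in unstated number.

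**Formulas.** P is the number of parameters and R² the Cox–Snell value.

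- Shrinkage: n = P / [(S − 1) ln(1 − R²/S)], with S = 0.9.
- Optimism: the same formula with S = R² / (R² + 0.05 × R²max). At 30% prevalence R²max = 0.705.

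The document gives no C-statistic, so C is an assumption shown over a range. It is converted to R² with a normally distributed linear predictor at 30% prevalence: C = 0.70, 0.77, 0.80, 0.85 and 0.92 give R² = 0.103, 0.186, 0.228, 0.307 and 0.439.

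Example, P = 22 and C = 0.77: 22 / [0.1 × −ln(1 − 0.1857/0.9)] = 22 / 0.02311 ≈ 952.

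**Patients required for 22 parameters:**

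| Assumed C | Shrinkage | Optimism | Larger of the two |
|---|---|---|---|
| 0.70 | 1,803 | 580 | 1,803 |
| 0.77 | 952 | 552 | 952 |
| 0.80 | 754 | 538 | 754 |
| 0.85 | 528 | 510 | 528 |
| 0.92 | 329 | 460 | 460 |

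Above C of about 0.92 the shrinkage criterion alone would be met, but the optimism criterion is not: it still needs 368 at C = 0.995.

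**Smaller counts.** With 17 parameters (one per variable) the requirement is 583 at C = 0.80 and 335 at 0.95. With only the blood flow measures (22 less thickness 1, morphology 2, motion 4 and volume 1, so 14) it is 480 at C = 0.80, and 323 suffices only from C of about 0.86.

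**What 323 supports** (the stricter of the two criteria). The training share is 0.7 × 323 = 226.

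| Assumed C | Parameters at n = 323 | Parameters at n = 226 |
|---|---|---|
| 0.70 | 3.9 | 2.8 |
| 0.77 | 7.5 | 5.2 |
| 0.80 | 9.4 | 6.6 |
| 0.85 | 13.5 | 9.4 |

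**The case against.** **The inputs may be in the supplement.** S1 Fig is not shown, and an article may leave inputs there. With nine predictors, the number in the cited study, 323 is a valid maximum over all three criteria once C reaches about 0.79. This stands. A reader might infer that only the average-risk criterion was run, or that the arithmetic is wrong; the document supports neither. What remains is that an input of about nine would not describe the features listed elsewhere in the article. If 76.92% were read as a C-statistic (it is an accuracy), nine predictors would need 393.

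**The count is a reader's count.** No section states 22, and the Discussion sentence covers blood flow parameters only. The variance and collinearity filters do not use the outcome and may reduce the count, by an unknown amount; several arterial indices derive from the same velocities. This partly stands. The Spearman screen does use the outcome, so variables it drops still count as candidates. Clinical features raise the count. A reader might also multiply the eight arterial indices by the four sampling sites and reach 46, but the article does not say that each site enters separately.

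**The formulas are for unpenalised regression.** A support vector classifier has its own regularisation. This stands: the figures are a benchmark, and the document does not support a statement that the classifier will be overfitted by a given amount. The benchmark is still relevant because the plan chose this tool.

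**All 646 patients might train one model,** as the abstract can be read. Study design and the sample-size section refer to RIF patients. Even with 646, and 30% assumed overall, 22 parameters need C of about 0.82.

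**Conclusion.** The point holds in a limited form. The figure 323 is correctly computed as the number that gives ±5 points on a 30% pregnancy rate. It may also be the correct tool output for a small model. It is not the minimum, by the tool's own criteria, for the features the plan lists: at assumed C-statistics of 0.77 to 0.85, 22 parameters need about 1.6 to 2.9 times as many patients (528/323 to 952/323). At C = 0.80, 17 parameters need 1.8 times as many (583/323).

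This rests on three assumptions: the C range, the parameter count before outcome-free filtering, and the use of regression criteria as a benchmark.

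There is a separate wording mismatch. The sample-size section says that "at least two failed ETs were diagnosed as RIF", whereas for unknown ploidy Diagnostic criteria for RIF patients says "RIF is diagnosed in female patients under 35 years old after three or more embryo transfers (ET" and sets higher numbers for older women; two applies to known ploidy. A reader might infer that the 30%, and hence 323, rests on the wrong population. The text does not tie the two together, so this does not bear on the number.

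**What to change.** Keep 323 and restate what it gives. Suggested content for the sample-size section:

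- 323 RIF patients estimate an overall clinical pregnancy rate of 30% to within ±5 percentage points.
- As a regression benchmark only, 323 patients support about 4, 7, 9 and 13 candidate parameters at C = 0.70, 0.77, 0.80 and 0.85, and the roughly 226 training patients about 3, 5, 6 and 9. The entries 4 and 3 are rounded up from 3.9 and 2.8.
- The anticipated C is an assumption, with its basis given, and the candidate count is stated with the result of all three criteria.

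Then pre-specify a primary candidate set of supportable size that includes the MV-FLOW index. Reduce the list without using the outcome, for example by dropping redundant arterial indices. Report the all-feature classifier as exploratory. Separately, reconcile the sample-size section's description of RIF with the diagnostic criteria.

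No further patients are needed. The cost is more than rewording: the sample-size claim becomes less favourable, and the primary analysis uses fewer features, so the search across all ultrasound indices for the most predictive one becomes a secondary, exploratory aim.
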